## Abstract

**Background:**

Anorexia nervosa (AN) mainly affects women (sex ratio 1/10) and most often starts during adolescence. The prognosis of AN remains poor (10% of deaths and high risk of chronicity). Body dissatisfaction, disturbances in recognition and identification of body sensations are some of the key symptoms of AN. However, there is a contrast between this consensual observation of body image disorders in AN, and the relative deficit of specifically targeted body treatments. Our proposal for a body approach specifically dedicated to AN is based on the understanding that posture, breathing, muscle tension and body perception are closely linked to our psychological and emotional state and are therefore disturbed in patients with AN. The purpose of this monocentric randomized controlled trial is to evaluate if a targeted osteopathic protocol treatment for AN in addition to treatment as usual (TAU) is significantly more effective than TAU alone.

**Methods:**

In total, 72 patients meeting the inclusion criteria will be randomly assigned to one of the two treatment groups: one receiving the specific osteopathic treatment targeted for AN in addition to the TAU (group A) and the other one, receiving TAU only (group B). The patients in group A will receive 5 30-min osteopathic treatment sessions. Soft specific palpatory techniques on the diaphragm, digestive system and cervical region will be performed. The TAU is defined by the multidisciplinary approach recommended by the French health high authority. The primary outcome is the evaluation of interoceptive sensibility and secondary outcomes include clinical and psychopathology-related symptoms with assessment of somatic dysfunctions’ evolution. A qualitative study will also be carried out, applying the Interpretative Phenomenological Analysis method. Patients will be included for a maximum of 14 weeks between the inclusion time and the last evaluation.

**Discussion:**

If the results of the study are positive (statistically significant efficacy of this osteopathic treatment protocol), the study will provide arguments in favor of osteopathic sessions as a possible non-invasive additional treatment option in the multidisciplinary care approach for patients with AN.

**Trial registration:**

ClinicalTrials.gov ID: NCT04666415, Release Date: December 11, 2020; N° ID-RCB: 2019-A02613-54.

**Supplementary Information:**

The online version contains supplementary material available at 10.1186/s13063-021-05810-8.

## Background and rationale

Anorexia nervosa (AN) is defined by the DSM-5 as a restriction of energy relative to requirements, leading to a significantly low body weight, an intense fear of gaining weight or becoming fat, as well as disturbances in the way in which one’s body weight or shape is experienced and/or lack of recognition of the severity of current low body weight [1]. AN is a psychiatric disorder included among eating disorders (ED), with a reported prevalence in women ranging from 0.5 to 2.2% [2–4]. The age of onset of AN is mostly between 14 and 24 years old, and in half of the cases before the age of 18 [5]. Among all ED, AN is the one with the worst prognosis, with mortality 6 to 12 times that observed in a comparable general population of the same age [4], in particular due to somatic complications related to undernutrition, multiple hospitalizations, psychiatric comorbidities (mood, anxiety, personality and addictive disorders) and a significant suicidal risk [2, 4, 6–8]. According to main international guidelines, an overall assessment is recommended, combining a somatic, nutritional, and psychological assessment, also including social and family dynamics. An individualized care network has to be built for the patient and adjusted to his needs according to the evolution. It is a complex management, which requires a close collaboration between somaticians and child psychiatrists and, if possible, a dietician or a nutritionist [9–11].

AN perfectly illustrates the complex links between soma and psyche. It has been associated with profound alterations of body experiences and representations [12–14]. The perception of body image is wrong, distorted, sometimes almost delusional with a lack of knowledge or even a denial of thinness. Hilde Bruch was one of the first to identify these disturbances in body awareness, and to emphasize the absolute need to help patients become aware of their body’s perception and sensations [15]. Hypertonicity, body rigidity, and postural disorders are frequently associated with anorexic disorders. Muscular posture and tension are indeed closely related to the psychological and emotional state. Emotional avoidance leads to restricted breathing (not fully involving the balance between diaphragm and abdominal muscles), anxiety is the cause of chronic muscle tension, social withdrawal leads to body attitudes folded on oneself, and an impoverishment of spontaneous bodily movements, lack of self-confidence leads to poor postural stability [15].

The notion of embodied cognition (embodiment) suggests that the perception and treatment of an emotion involves its perceptive, motor, and somatovisceral experience [16, 17]. Interoceptive awareness describes behavioral, metacognitive, and cognitive processes related to internal bodily perceptions. Related to that concept, various studies showed behavioral interoceptive deficits in AN subjects with reduced interoceptive accuracy (that is, the ability to correctly perceive the internal sensations of the body) and also reduced interoceptive sensitivity (beliefs related to internal perceptions evaluated through questionnaires) [18, 19]. Alteration of the interoceptive consciousness could thus contribute to the symptoms of AN, for example the altered experience of hunger and satiety [20, 21], body image distortion, and alexithymia [18, 22].

Body-oriented care (relaxation, psychomotor therapy, aesthetic care, massage) is used in the care for patients suffering from AN [23]. The body approach and body image therapies allow adolescents to reinvest their body perceptions and sensations other than through deprivation and suffering and contribute to the improvement of their health status. It helps the adolescent break the body-mind division and the massive denial in which she/he is locked [23]. Unfortunately, studies on body-based approaches in AN are sparse and include small cohorts. They show little effect on weight evolution but a possible decrease in anxiety, frequent improvement of the thymia, and reduction in dietary concerns [24]. In addition, Adaptive Physical Activity Programs allow for progressive stress rehabilitation and have demonstrated beneficial action on the evolution of symptoms, particularly an improved self-perception [23].

There is a contrast between this consensual finding of the importance of body pattern disorders and body perception in AN, and the relative deficit of specifically targeted body care for AN. The body approach that we propose is based on the understanding that posture, breathing, muscle tension, and body perception are closely related to our psychological and emotional state, and therefore are disturbed in a patient suffering from AN. In osteopathic medicine, the osteopath, in a systemic approach after osteopathic diagnosis, carries out mobilizations and manipulations for the management of osteopathic dysfunctions of the human body.

To date, to our knowledge, there is no study based on the evaluation of an osteopathic treatment protocol in the management of patients with AN. Studies have focused on the contribution of osteopathy to intestinal functional disorders. Several studies have shown decreased abdominal pain in populations with chronic constipation [25] and irritable bowel syndrome [26, 27]. Another study showed improved abdominal pain and bloating, decreased use of medication, and improved quality of life for women with functional constipation after osteopathic treatment at a rate of one session per week for 1 month [28].

Thus, the ACAMTO study is exploratory research which aims to evaluate the impact of a targeted osteopathic treatment for AN within the framework of the recommended multidisciplinary approach for anorexic adolescent population.

## Objectives

### Primary objective

The main objective of this randomized parallel-group trial is to examine if the addition of a targeted osteopathic treatment to treatment as usual (TAU) for AN (multidisciplinary treatment program for adolescent with AN) is significantly more efficacious than TAU alone in terms of interoceptive sensitivity.

### Secondary objectives

Secondary objectives are as follows:
To examine if adding a targeted osteopathic treatment to TAU for AN is significantly more efficacious than TAU alone in terms of clinical evolution, evaluated by other clinical outcomes (self-esteem, anxiety, depression, depressivity, alexithymia, quality of life, ED symptoms, physical hyperactivity, self-injury, body satisfaction, body mass index).To assess if adding a targeted osteopathic treatment to TAU for AN compared to TAU alone is significantly more efficacious in terms of the evolution of somatic dysfunctions (sensitivity, mobility, texture, asymmetry).To explore the subjective experience of patients who have completed osteopathic treatment sessions.To explore the subjective experience of osteopath students who have performed the osteopathic treatment sessions.

### Hypotheses

We developed, within the department of Psychiatry, a specific body approach for female adolescents hospitalized for AN. In collaboration with an experienced osteopath, [name], we will offer an osteopathic treatment of 5 sessions performed over a week, in addition to the usual care offered to these patients. This approach is designed to enable anorexic teenage girls to improve their body perception and better embody their own body.

The hypothesis of this research is that a specific body approach to AN, based on osteopathic treatment sessions, in addition to the TAU, is significantly more efficacious than the TAU alone.

## Methods

### General design aspects

This study is an exploratory add-on, monocentric, prospective, parallel-group, randomized controlled trial comparing a targeted osteopathic treatment in addition to TAU (multidisciplinary treatment program for adolescent with AN) versus TAU alone. Participants will be randomly allocated to either receive the 5 30-min sessions of osteopathic treatment spread over a week plus the TAU for AN (Group A) or receive the TAU alone (group B). Outcomes will be assessed at baseline, before the 3rd osteopathic session (group A) or 3 weeks after the first questionnaires (group B), and 1 week after the last osteopathic session (group A) or 6 weeks after the first questionnaires (group B). Patients will be included for a maximum of 14 weeks between the inclusion time and the last evaluation. The study protocol is outlined in the flowchart (Fig. 1).

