#### Osteopathic treatment (group A)

Special attention is paid to body approach care for anorexic patients in our psychiatry unit. A targeted osteopathic treatment for AN has been created by an osteopath ([name]), based on scientific literature and her own experience. The protocol was refined after 3 sessions for 3 different patients during the preparatory phase of the study. Indeed, in May 2019, 3 sessions of the osteopathic protocol were performed 1 week apart for 3 patients hospitalized in the department of psychiatry, after medical advice of no contraindication to the practice. The consent agreements of patients and their parents were collected and included in their medical records. Each intervention took place in full view of a caregiver of the unit as we usually do.

The osteopath, [name], trained and supervised a group of osteopath students specially dedicated to the protocol, in their 3rd and 4th year of school.

Each patient allocated to group A will be followed by the same two osteopaths. One of them will provide the 5 sessions of osteopathic treatment. Sessions have a 30-min duration and about a week separates two sessions. The other one will evaluate the evolution of the somatic dysfunction. Two caregivers of the service will attend the sessions with the osteopaths and the patient. The presence of a caregiver during the therapeutic activities is customary in our unit.

The osteopathic treatment protocol will use techniques on 3 areas: cervical, diaphragmatic, and digestive. The protocol is detailed in Additional file 2.

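### Group A's T2 and T3 follow the treatment sessions and group B's follow the calendar, and the text contradicts itself on session spacing, so follow-up length need not be equal in the two arms

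*Protocol article*

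**What the plan says.** **Assessment times.** General design aspects places T2 "before the 3rd osteopathic session (group A) or 3 weeks after the first questionnaires (group B" and T3 "1 week after the last osteopathic session (group A) or 6 weeks after the first questionnaires (group B". The Instruments section repeats both definitions, and Secondary outcomes repeats the one for T3. The primary outcome is the last fMAIA value minus the first, so the T1–T3 interval is the period that the primary change score covers.

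**Session spacing.** Three places describe it:

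- Hypotheses: "we will offer an osteopathic treatment of 5 sessions performed over a week".
- General design aspects: group A will "receive the 5 30-min sessions of osteopathic treatment spread over a week".
- Osteopathic treatment (group A): "Sessions have a 30-min duration and about a week separates two sessions". The same section reports that the three preparatory-phase sessions were given a week apart.

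**Limits on timing.** The only bound in the text is "Patients will be included for a maximum of 14 weeks between the inclusion time and the last evaluation". The text shown gives no interval from the first questionnaires to session 1 and no visit window.

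**Analysis.** The Statistical methods section compares change scores by a t test or a Mann-Whitney test and states that no adjusted analyses are planned.

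**The concern.** A change score compares treatments fairly only if it spans the same period in each arm. Here the period is set by one rule in group A and by another in group B. Group A's rule depends on when the last session takes place, which is decided after randomization.

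Time matters in this population. Both arms receive active multidisciplinary care, and inpatients are treated under a contract built on weight targets. Weight, mood and possibly interoceptive sensitivity can move with time alone. If one arm is seen sooner or later than the other, that movement is mixed with the treatment effect, and an unadjusted test cannot separate the two.

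The contradiction on spacing is more than an editorial slip, because T3 in group A hangs on the last session. Until the spacing is settled, the timing of the primary endpoint in one arm is not defined by the text.

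**Working it through.** **Inputs**

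- Five sessions; T2 in group A just before session 3; T3 in group A one week after session 5 (General design aspects).
- Group B: T2 at 3 weeks and T3 at 6 weeks (General design aspects).
- *s*, weeks between sessions: 1 under the section on the osteopathic treatment. If all five fall on days 0 to 6, as Hypotheses and General design aspects imply, *s* = (6/7)/4 = 0.214.
- *L*, weeks from T1 to session 1: not given in the text shown, so it is an assumption and is varied.

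**Formulas for group A**, with equal spacing:

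T2 = *L* + 2*s*; T3 = *L* + 4*s* + 1.

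**Step 1: can group B's 3 and 6 weeks be reproduced in group A?** Set *L* + 2*s* = 3 and *L* + 4*s* + 1 = 6. The second gives *L* + 4*s* = 5. Subtracting the first gives 2*s* = 2, so *s* = 1 and *L* = 1. Both visits coincide with group B's only if sessions are weekly and start one week after T1.

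**Step 2: other combinations**

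| Session spacing | *L* (weeks) | T2, group A | T3, group A | T3 difference from group B |
|---|---|---|---|---|
| Weekly | 0 | 2.0 | 5.0 | −1.0 |
| Weekly | 1 | 3.0 | 6.0 | 0 |
| Weekly | 2 | 4.0 | 7.0 | +1.0 |
| All five in 7 days | 0 | 0.4 | 1.9 | −4.1 |
| All five in 7 days | 1 | 1.4 | 2.9 | −3.1 |
| All five in 7 days | 2 | 2.4 | 3.9 | −2.1 |
| Every 10 days (slippage) | 1 | 3.9 | 7.7 | +1.7 |
| Every 14 days (slippage) | 1 | 5.0 | 10.0 | +4.0 |

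The last two rows are illustrations of delay, not schedules found in the article. They show that slippage moves T3 in group A and leaves group B at 6 weeks.

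**Step 3: the upper bound.** The 14-week limit is counted from inclusion. It allows 14 − 6 = 8 weeks beyond group B's T3 only if T1 coincides with inclusion. Otherwise the possible T1–T3 interval is shorter.

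**Step 4: size of any bias.** This needs the rate at which fMAIA changes under usual care. The article gives no such figure, so the bias cannot be calculated from it.

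**The case against.** The best defence is that matched timing was intended. The intervention section speaks of about a week between sessions, the preparatory sessions were a week apart, and group B's 3 and 6 weeks are exactly what weekly sessions starting one week after T1 would give. On that view the phrase in the other two sections is loose wording for one session per week, and the arms are aligned as planned. The interval to session 1 and the visit windows may stand in the full protocol, or in the two figures that are not shown. The trial also calls itself exploratory.

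Much of this stands. It makes the gap of about 4 weeks the less plausible reading, and the absence of windows from an article is not a fault in itself. It does not remove two things. The statements on spacing still conflict, and no figure can make both true. And even a perfectly aligned plan holds only while every session is on time, because group A's visits move with the sessions and group B's do not.

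A fair point can also be made against the remedy. Assessing one week after the last session measures the effect after a completed course, whereas a calendar visit may come before that course ends in a delayed patient. That is a real trade-off, and it is counted as a cost of the fix.

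**Conclusion.** The point holds as a possible bias together with an internal contradiction, and it should be fixed. As written, the T1–T3 interval in group A is not determined by the text. It runs from about 2 weeks (all sessions within a week, session 1 at T1) to 5 or 6 weeks (weekly sessions, session 1 at T1 or a week later), and longer with delay, against 6 weeks in group B. Every group A figure rests on an assumed interval from T1 to session 1. The direction of any bias is unknown.

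A reader might infer more than the article supports:

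- **An inflated false-positive rate.** If one assumes a drift of 0.025 to 0.05 SD per week, a 4-week gap gives a spurious difference of 0.10 to 0.20 SD. With 33 per arm the standard error is √(2/33) = 0.246 SD, and the two-sided rejection rate is 6.9% to 12.8%. But the drift is invented, and the 4-week gap needs the less plausible spacing. A 1-week gap at the upper drift gives 0.05 SD and about 5.5%, close to the nominal 5%.
- **Follow-up of 14 weeks against 6.** The limit runs from inclusion, so it is a T1–T3 bound only in the special case shown in the working.
- **Unblinding.** Visits triggered by sessions might hint at allocation, but the article does not say that the research psychologist learns what triggers a visit. Patients know their group in any case, and the fMAIA records their own beliefs.
- **Early T3 for patients who stop treatment.** The text shown gives no rule for partial attendance, so this is inference.

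**What to change.** 1. Schedule T2 and T3 in both arms at the same elapsed time from T1, with the same window, whatever number of sessions has been attended. The 3 and 6 weeks already used for group B would serve. Planned follow-up is then equal by construction.
2. Record the actual number of days from T1 to each assessment for every patient. Recruitment has already begun, so this also lets the timing be described for patients already enrolled.
3. Reconcile the Hypotheses and General design aspects sections with the section on the osteopathic treatment. The sponsor decides which schedule is correct.

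The cost is protocol wording and visit scheduling. The downside is that a group A patient whose sessions are delayed may be assessed before the last one.

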**Fig. 1 Fig1:**
[figure not shown]
ACAMTO study participants flowchart. Legend: TAU = treatment as usual; T = time

The Standard Protocol items: Recommendations for Interventional Trials (SPIRIT) checklist is provided in Additional file 1.

### Participants

Patients will be recruited from the inpatient and outpatient units of the Adolescent and Young Adult Psychiatry department of the Institut Mutualiste Montsouris (Paris, France).

#### Inclusion criteria

All patients treated in outpatient care or hospitalized for AN in the psychiatry unit of the Institut Mutualiste Montsouris will be offered by the principal investigator or co-investigators to participate in the study if (1) they are female, (2) they are aged between 13 and 20 years old included, (3) they have a Diagnostic and Statistical Manual of Mental Disorders fifth edition (DSM-5) diagnosis of AN (restricting or binge-eating/purging types), (4) they have a body mass index (BMI) ≥ 14 kg m^−2^, (5) they have been treated in consultation for at least 2 months or have been hospitalized in the psychiatry unit of Institut Mutualiste Montsouris, (6) they have a clinical/somatic state compatible with osteopathy sessions (prior medical advice), (7) they are not in a “separation period”, (8) they have signed the informed consent form as well as both parents for patients under 18, and (9) they are not part of another research protocol.

At the Adolescent and Young Adult Psychiatry department of the Institut Mutualiste Montsouris, during a full-time hospitalization for AN, the “separation period” is linked to the establishment of a hospitalization contract between the medical team, the family, and the patient. This contract defines a time of separation between the family and the patient. It is built around two axes: the final discharge weight allowing the patient to leave the service and an intermediate weight called the “separation lifting weight.” This separation lifting weight is so named because it puts an end to the first part of the hospitalization which is carried out away from the living environment of the patient (parents, friends, schooling…).

#### Non-inclusion criteria

Patients will not be included in the study if (1) they are male, (2) they are under 13 years old or over 20 years old, (4) they have a contraindication to osteopathic body approach sessions (fracture, recent surgery, etc.), (5) they have a body mass index (BMI) < 14 kg m^−2^, (6) they need a naso-gastric tube, (7) they are in a “separation period”, (8) they are not fluent in French, (9) they are not covered by health insurance, and (10) they are part of another research protocol.

Non-included subjects will be listed along with the causes of their non-inclusion.

#### Exclusion criteria

Patients will be excluded from the research if (1) they have a contraindication to osteopathic body approach sessions (fracture, recent surgery, somatic state not compatible with the osteopathic treatment), (2) they are not covered by health insurance, and (3) they are part of another research protocol. Excluded subjects will be listed along with the causes of their exclusion.

#### Randomization

All patients who give consent to participate and who fulfill the inclusion criteria will be randomized. Randomization will be centralized and stratified according to the status of treatment at inclusion (outpatient care or hospitalization) and age (2 classes: 13–15 years old included and 16–20 years old). A randomization list with blocks of variable sizes will be computer-generated by a statistician independent from the group recruiting the patients and the group taking care of patients. The allocation ratio will be 1:1.

